### Expected outcomes

The environmental impacts (climate change, water consumption and water scarcity) are higher in FF compared to EBF and MF.The environmental impacts (climate change, water consumption and water scarcity) due to an increase in maternal diet to compensate for breastfeeding are insignificant.

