The manufacture and distribution of industrial infant formula is harmful to the environment, generates polluting waste, and requires energy use to manufacture the formula and packaging materials, and to transport the products, and water use to prepare bottles on a daily basis. Most infant formulas are based on cow's milk. Dairy farms represent the main source of anthropogenic methane emissions. In Europe, livestock farming represents 12–17% (630–863 Mt CO_2_-eq) of total GHG emissions [8].

For an accurate calculation of the environmental impact of breastfeeding, the infant feeding accessories (breast milk pump; milk storage containers or bags, bottles, bottle warmer, and bottle sterilizer, for example) and a theoretical increase of 500 kcal in the diet of the mother must be taken into account [1, 9–12].

There is data on the carbon footprint and water footprint of FF, but there is none on the environmental impact of breastfeeding. The average carbon footprint of FF was estimated to be 9.2, 7, 8.4, and 11 kg CO_2_-eq per kg of formula in New Zealand, USA, Brazil, and France, respectively. The potential carbon savings of BF compared to FF for the UK, China, Brazil and Vietnam is 40–55% [1].

The additional volume of water that a mother consumes while breastfeeding is minor compared to the significant quantities needed for manufacturing formula milk [12]. Research conducted by Pope et al. in the United States demonstrated that producing 1 kg of commercial formula requires 6.6 kg of raw milk, which entails a water footprint (WF) comprising 626 L of blue water for manufacturing, reconstitution, and sterilization, 6,280 L of green water for cow feed, and 524 L of grey water [13]. In Switzerland, Rollins and colleagues estimated that the average WF for whole cow's milk is around 940 L of water per kg of raw milk. When considering that 1 kg of whole milk produces about 200 g of milk powder, the water consumption (WC) amounts to 4,700 L of water per 1 kg of milk powder [14, 15].

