### Sample size calculation

For the calculation we took into account both the local data on prevalence of three infant feeding types at month 1 [21] and the data provided by the literature for the footprint for consumption of 1 kg powdered breastmilk substitute for the nearest geographical area. This is 11 kg CO2 equivalents and standard deviation 1 in UK/France [1]. Accepting an alpha risk of 5% and a power of 80%, in a two-tailed test, a minimum of 60 subjects are necessary in the EBF group, 60 in the mixed and in 30 in the FF group to recognize as statistically significant a difference greater than or equal to 0.7 units (One-Way ANOVA menu, StudySize 2.0) [28]. The common standard deviation is assumed to be 1 [1] (One-Way ANOVA menu, StudySize 2.0, [28]).

These 150 women (60 + 60 + 30) are the minimum number we need to recruit. However, at the time of recruitment, we do not know which breastfeeding arm each of the participating women will be in during the follow-up month. From our own previous studies [21], we know that after one month of follow-up, from an initial recruitment of 400 women, some 256 (64%) could be breastfeeding exclusively, 92 (23%) using mixed and 52 (13%) a formula feeding [21]. These expected female counts exceed the required minimums in each arm, and would allow replacement rates for losses during follow-up of up to 35%.

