**Fig. 1 Fig1:**
[figure not shown]
Environmental impact factors considered in the GREEN MOTHER I project. Legend: EBF – exclusive breastfeeding; MF – mixed feeding; FF – formula feeding

For the descriptive statistics, the qualitative variables will be described with their absolute and relative frequencies and quantitative variables with their mean and standard deviation or with their median and quartiles. In the comparison of proportions, we will use the Pearson Chi Square test and in the comparisons in quantitative variables the analysis of variance or the Kruscal-Wallis test (with post-hoc analyses), depending on the conditions of application. The level of significance will be 5% and the analyses will be performed with the statistical package STATA v.18.

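### The expected finding that the diet impact of breastfeeding is insignificant has no definition, and the stated difference tests at 5% cannot support it

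*Protocol article*

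**What the plan says.** Expected outcomes lists two forecasts. The second is that the impacts on climate change, water consumption and water scarcity "due to an increase in maternal diet to compensate for breastfeeding are insignificant". The article does not say whether the last word means statistically non-significant or small in size, and it attaches no threshold in kg CO2eq, m3 or m3eq.

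The Data analysis plan specifies "in the comparisons in quantitative variables the analysis of variance or the Kruscal-Wallis test (with post-hoc analyses), depending on the conditions of application", with significance set at 5%. It also plans means with SDs or medians with quartiles, and it presents the impact of feeding type with accessories separately from the impact of the mother's diet.

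Sample size calculation gives "a minimum of 60 subjects are necessary in the EBF group, 60 in the mixed and in 30 in the FF group" in order to detect "a difference greater than or equal to 0.7 units". The SD of 1 comes from the footprint of 1 kg of formula powder. Nothing is sized for maternal diet.

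Background explains why diet is in the study: "a theoretical increase of 500 kcal in the diet of the mother must be taken into account". Data collection places the maternal nutrition questionnaire at the 4–6 week visit only, and Study Limitations confirms one recall day per woman.

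**The concern.** The forecast is a near-null statement, and the named tests are built to reject equality. A p-value above 0.05 from analysis of variance or Kruskal-Wallis does not show that an effect is small. It is also what a noisy measurement or a small group produces. In the other direction, a trivial difference could reach significance and appear to contradict the forecast. The stated tests therefore do not answer the question in either direction.

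The word increase is a second difficulty. With no diet record before lactation, no change within a woman is measured. The data can give only a difference between women who lactate and women who do not. FF is the smallest group, and one recall day carries day-to-day variation.

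What is at stake is the diet-only statement. Background says that no data exist on the environmental impact of breastfeeding, so whether extra maternal food offsets part of the saving on formula is one of the study's new questions. The results are to feed the Phase II guide and public material.

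**Working it through.** **1. The plan's own figure.** Inputs from Sample size calculation: groups 60/60/30, range of means 0.7, SD 1, two-sided alpha 5%, power 80%. Take evenly spaced means 0, 0.35, 0.7 for EBF, mixed feeding (MF) and FF. The weighted mean is (60×0 + 60×0.35 + 30×0.7)/150 = 0.28. The non-centrality is 60×0.28² + 60×0.07² + 30×0.42² = 10.29. With F(2, 147), power is 81.9%. The stated size reproduces, but for a 0.7-unit difference on the formula-footprint scale, not for diet.

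**2. Group sizes for a diet contrast, EBF v FF.**
- Minimum: 60 v 30.
- Expected: 256 v 52 (64% and 13% of 400).
- After the 35% loss that the article allows for: 256×0.65 = 166 and 52×0.65 = 34.

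**3. Chance of a non-significant result.** The article gives no SD for diet impact, so differences are in SD units and are assumptions. SE = √(1/n1 + 1/n2). Power is from the non-central t with non-centrality d/SE, two-sided 5%. Half-width is t(0.975)×SE.

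| EBF v FF | SE | 95% CI half-width | Non-sig. at 0.2 SD | at 0.3 SD | at 0.5 SD |
|---|---|---|---|---|---|
| 60 v 30 | 0.224 | 0.44 SD | 86% | 74% | 40% |
| 166 v 34 | 0.188 | 0.37 SD | 82% | 65% | 25% |
| 256 v 52 | 0.152 | 0.30 SD | 74% | 50% | 9% |

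At 256 v 52, power is 75% at 0.4 SD. The difference detectable with 80% power, (1.96 + 0.84)×SE, is 0.63, 0.53 and 0.43 SD in the order of the table.

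Pooling EBF and MF against FF, as the calorie objective does, changes little because FF limits precision. At 0.3 SD, non-significance is 69% (120 v 30), 63% (226 v 34) and 48% (348 v 52).

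**4. A case where power is good.** If the full 500 kcal difference exists, power on kcal at 60 v 30 runs from 79% (assumed SD 800 kcal) to nearly 100% (assumed SD 400 kcal). At 256 v 52 it is 98% to 100%. The risk therefore concerns small or moderate differences.

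**5. What a negligibility rule could deliver.** For a true difference of 0 and margin m, the chance that the 95% interval lies inside ±m is about 2Φ(m/SE − 1.96) − 1. At 256 v 52:
- m = 0.5 SD: 0.5/0.1521 = 3.29, giving 82%.
- m = 0.3 SD: 0.3/0.1521 = 1.97, giving 1%.

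With two one-sided 5% tests (the 90% interval; 1.645 in place of 1.96) the figures are 90% and 26%. At 166 v 34 and m = 0.5 SD they are 51% and 69%. A wide margin is within reach at the expected counts. A tight one is not.

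**The case against.** The strongest reply is that this is a forecast and not a decision rule. The Hypothesis section says only that EBF will have the smaller impact. No sentence says that p > 0.05 will be read as no impact, and the forecast may simply mean small in magnitude. That stands. A reader might infer that lack of power will be reported as absence of impact, but the article does not say so. What remains is that neither meaning is usable as written: the statistical one is invalid inference, and the magnitude one has no threshold.

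A reader might also infer that a mistaken verdict on diet would overstate the net benefit of EBF. The article does not support that. Under Procedure, measured diet is added to accessories and formula in every group's total, and nothing removes diet if it is non-significant.

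Third, descriptive estimates are planned and the diet component is shown separately, so its size will be visible. That also stands, but it supplies no rule for calling the size negligible.

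Finally, confidence intervals and margins may sit in a full protocol or SAP that is not shown. Their absence here is therefore not the point. The point is that this article states a near-null expectation next to methods that cannot support it.

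**Conclusion.** The point holds at moderate severity. The expected outcome is undefined, the stated tests cannot establish it, and the design measures a between-group difference and not an increase. If non-significance were taken as support, a true EBF–FF diet difference of 0.3 SD would pass as insignificant in about half of studies at the expected counts, and in up to about three-quarters at the minimum.

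These percentages rest on an assumed effect in SD units, roughly normal data and an unadjusted two-group comparison at 5%. They fall quickly for larger effects: at 256 v 52, 25% at 0.4 SD and 9% at 0.5 SD. It would be too strong to say that non-significance is the likely result in general. The logical point, that a difference test cannot show negligibility, depends on none of these assumptions.

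**What to change.** Reword the second expected outcome as an estimate: the between-group difference in diet-only impact per day, EBF minus FF and EBF plus MF minus FF, with a 95% confidence interval for each of the three indicators. Show it beside the formula-plus-accessories impact in the same unit, so that the reader can see how much of the saving diet could offset. Call it a difference between groups, not an increase.

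State that p > 0.05 will not be read as insignificant. Use the word negligible only if the interval lies within a margin fixed before analysis for each indicator, for example a stated share of the FF formula-plus-accessories impact. Otherwise report the result as inconclusive. If no margin can be justified, present the outcome as estimation only.

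The cost is wording and one margin per indicator, with no new data. The price is that the diet question may have to be reported as inconclusive, which step 5 of the working makes likely for a tight margin.

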### Ethics and safety

The study follows the guidelines of the Declaration of Helsinki regarding the bioethical principles of clinical research. The research protocol has been approved by the Research Ethics Committee (CEI) of the Jordi Gol Institute of Primary Care Research (IDIAP), as well as those of the reference hospitals participating in the study: Hospital Parc Taulí, Hospital General de Granollers, Hospital Germans Trias i Pujol and Hospital de Mataró.

The data collected by questionnaires on REDCap are to be encrypted. The variables needed to conduct the study have been obtained directly from the project participants through their consent, in accordance with the provisions of Articles 6.1.a) and 9.2.a) of the GDPR.

The REDCap platform is used to carry out the project. It is hosted on the institution's servers and its security measures are determined by the institution. The data is stored on the local web server where the institution has installed the software and is therefore only accessible on computers that have a trusted connection to it via VPN (Virtual Private Network) and secure credentials (certificates, RSA keys or complex passwords). A system has been incorporated so that only the application service can send data to the back office through a firewall that only allows requests from the application's IP addresses. The web server has the X-Frame-Options HTTP header setting enabled with the value "same-origin" to prevent clickjacking attacks.

Compliance with the Patient Autonomy Law is ensured and the data are collected anonymously in compliance with EU regulation 2016/679. The ICS is the data controller and the current study data owner.

## Discussion

The main aims of this study (Phase I) are to explore: 1) environmental impacts of three types of infant feeding including accessories used and maternal diet; 2) characteristics of maternal diet with food consumption habits and 3) socio-demographic and clinical factors associated to three infant feeding types. As per the results of this study, a report will be drawn up with environmental data on the mothers' diet and the accessories used during infant feeding. This will also serve as the basis of the documentation for the following GREEN MOTHER Phase II to evaluate the effectiveness of a multimodal educational and support intervention on EBF prevalence, diet and the environmental impact of different types of infant feeding.

For this intervention, we create the following resources:A Guide on best practices in breastfeeding, nutrition and sustainability based on scientific evidence that will serve to unify criteria and update knowledge for midwives and other health workers.Other informative tools (posters, leaflets, video tutorials) for excellence and best practices in breastfeeding care and sustainable nutrition will be prepared and disseminated among professional communities to create environmental awareness both in health workers and the general public at the national level.

### Strengths of the Study

To the best of our knowledge, this research represents the first endeavour of its nature in Spain, boasting a considerable sample size of 429 participants. It furnishes authentic insights into the behaviours of postpartum mothers throughout the initial month of their infants' lives, scrutinized through the lens of sustainability. This investigation has potential to guide mothers in their choices concerning infant feeding, acknowledging the smaller environmental footprint associated with breastfeeding.

### Study Limitations

The usual recommendation for 24-h dietary recall at the individual level is three days. In our case, as data is analysed in an aggregate manner, without carrying out intrapersonal analysis, recording one day seems the best option for adapting the research which intends to collect the minimum amount of data necessary to fulfil the objectives. Moreover, we have high risk of losing participants, attributable to the peculiarities of the vital period under study and the oversaturated care demands in the public health System.

### Dissemination

The results will be disseminated in the professional community and general public through continuing education courses, talks, colloquiums in the community, and presentations at conferences and congresses.

We plan to prepare three scientific articles:1 article on Protocol (Phase I), the current one2 articles on the results: 1) on the infant feeding type prevalence and maternal diet at 1 month of postpartum in journals in the field of nutrition and health and 2) the environmental impact of infant feeding to be sent to multidisciplinary journals on infant feeding, nutrition, health and environmental protection.

Moreover, we plan to present our projects and results in scientific conferences for health professionals in the region, at local and state level, annual meetings of gynaecologists and midwives, in the annual congress of midwives and congresses on primary care.

## Data Availability

Not applicable.
